### Participants and recruitment

#### Patient cohort

Patients diagnosed with active pulmonary TB are eligible to participate in this study before their treatment initiation between July 2018 to December 2020. Pulmonary TB should be confirmed by acid-fast bacilli (AFB) smear microscopy, sputum culture, and chest radiograph. Conventional drug-susceptibility testing (DST) and advanced line-probe arrays (LAPs) will be applied to test the susceptibility level of *M. tb* isolates. The inclusion and exclusion criteria are listed below.

#### Inclusion criteria

Patients diagnosed as active pulmonary TB based on bacteriological resultsPatients willing to receive hospitalized treatment for the first 2 weeksTreated with standardized FLDs regimenAged 18–65 yearsWritten informed consent

#### Exclusion criteria

PregnancyDiagnosed gastrointestinal diseasesSevere liver or renal dysfunction or diseaseHistory of antibiotic intake in the past 3 months before TB diagnosisDST-confirmed MDR (resistant to both INH and RFP)

#### Healthy controls

Healthy controls will be selectively enrolled from the local population during the routine health check-up. The inclusion and exclusion criteria are summarized below.

#### Inclusion criteria

No active TB diseaseNo history of TBAged 18–65 years

#### Exclusion criteria

PregnancyDiagnosed gastrointestinal diseasesSevere liver or renal dysfunction or diseaseHistory of antibiotic intake in the previous 3 months

### Sample size

Because of the absence of prior data on the study aims of the microbiota in a cohort study design of this topic, a pragmatic approach is chosen to determine the sample size. Based on the previous collaboration with the study sites, each site should enroll 50 eligible TB patients every year so that a patient cohort of 300 cases is expected within 2 years. Referred to the treatment failure rate (10%) in China [1], 30 patients in the conducted cohort are estimated to have unfavorable treatment outcomes. The sample size of microbiota study is usually selected empirically, a wide range of study settings indicates that 30 patients each group would likely be sufficient to assess phenotypic heterogeneity at the molecular level [21, 22].

Healthy controls will be equally recruited from the population taking routine health check-up in Sichuan and Shanghai with a total amount of 60. By assuming the rates of intestinal flora dysbiosis are 20% in TB patients [11] and 5% [23] in healthy controls [23], the sample size of 200 TB patients and 60 healthy controls has over 85% power to detect a significant difference in the composition of gut microbiota at the 5% significance level.

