## Background

Tuberculosis (TB), caused by *Mycobacterium tuberculosis* (*M. tb*), has plagued humans for thousands of years and remains a major public health problem. Estimated by the World Health Organization (WHO), there were 10 million TB cases and 1.6 million TB deaths worldwide in 2017 [1]. Among them, 890,000 new TB cases (8.9%) were infected in China, with a mortality rate of 26/100,000 [1]. TB is a curable disease, and the modern TB control program recommends the strategy of directly observed treatment – short-course therapy, which is a six-month standardized treatment using first-line anti-TB drugs (FLDs) including Isoniazid (INH), Rifampicin (RFP), Pyrazinamide (PZA), and Ethambutol (EMB). This potent standardized drug regimen has contributed to an up to 90% cure rate in TB patients during the last three decades. However, the high rate of recurrence and retreatment among TB patients, the ubiquity of severe gastrointestinal adverse reactions [1, 2], and the increasing epidemic of multidrug-resistant tuberculosis (MDR-TB) all suggest that the effectiveness of anti-TB treatment in China has yet to be addressed.

Therefore, introducing new knowledge and clinical strategies to improve the therapeutic effect and clinical prognostics in Chinese TB patients is of great significance. The recent research advances in gut microbiome have shown that these bacteria are not only actively involved in the absorption of food and drugs but also produce bioactive compounds influencing the immune and hormone systems, which is essential to maintain vital functions of the healthy host [3]. Generally, the human gut microbiota shows a large degree of interpersonal diversity [4], and its composition is also affected by many factors such as geography, diet, season, lifestyle, disease state, and in particular, the use of antibiotics [3, 5].

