### Study design

This study is an ongoing multicenter, population-based prospective cohort study conducted in three TB designated hospitals in Eastern and Western China. The study aims to include 300–400 bacteriologically confirmed pulmonary TB patients. Baseline information, including demographics, socioeconomic status, laboratory tests, and disease profiles, as well as sputum and stool samples will be collected from the enrolled patients immediately after TB diagnosis. The patient cohort will be built and followed up during the first-line anti-TB treatment at Day-14, Month-2, Month-5, last day of treatment, and the sixth month after treatment. Information regarding adverse effects, disease progress, and laboratory results will be collected at each visit. Stool samples will be sent to the laboratory for 16S ribosomal ribonucleic acid (rRNA) gene sequencing to identify the alterations in gut microbiota. A comparison of gut microbiota will be performed between newly diagnosed TB patients and healthy controls to reflect the difference in baseline features. After treatment completion, a nested case-control study will be performed between patients with treatment success or failure and patients with or without adverse effects to screen the potential biomarkers from the gut microbiota indicative of therapeutic effect.

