### Settings

Considering the differences in dietary habits, local economy and TB epidemic, patient recruitment for this study will take place at three geographic locations, i.e. Sichuan province, Jiangsu province, and Shanghai.

Shanghai (30°N 120°E) is an international metropolitan city in China with an estimated 24 million residents [16], first-ranked per capital disposable income and lowest TB report rate (14.75/100,000) in 2017 (Table 1) [17]. As one of the richest provinces in China, Jiangsu is located on the eastern coast of China next to Shanghai with the middle level of TB epidemic (33.52/100,000 [18]). On the contrary, Sichuan is an inland province located in Western China. Compared to the other two study sites, the income level, sanitation condition and health resources in Sichuan are less developed [16]. The notification rate of TB in Sichuan was 69.41 per 100,000 in 2017 [19], higher than the average level in China [20]. Regarding the dietary habits, Sichuan is famous for spicy food and high salt intake while people in Shanghai and Jiangsu prefer the light and sweet taste.

**Table 1 Tab1:** Economy, health resources and tuberculosis epidemic in study sites in 2017

Study sites	Per capita GDP^a^($)	Per capita disposable income ($)	Medical technical personnel in health care institutions (per 1000 persons)	Notified TB^b^ incidence rate (per 100,000 persons)
Sichuan	6671	2980.12	6.39	69.41
Jiangsu	16,010	5071.75	6.82	33.52
Shanghai	18,931	8541.93	7.73	14.75

^a^*GDP* Gross domestic product, ^b^*TB* Tuberculosis

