#### Microbiome analysis

The raw 16S rRNA gene data will be processed to generate amplicon sequence variants (ASVs) using DADA2 program [25]. Taxonomies will be assigned using Silva [26] as the reference database. Alpha diversity (such as Observed ASVs, Chao1, Shannon, Simpson, etc.) and beta diversity measures will be analyzed using QIIME2 [27] and the Wilcoxon and Kruskal–Wallis tests will be used for statistical testing of two and multi-group comparisons, respectively. Principal coordinate analysis will be used to interrogate the robustness of group-wise clustering, and Adonis test will be used to estimate statistical significance of group-wise beta diversity [27]. Generalized linear model (GLM) will be performed to evaluate the influence factors that may affect the gut microbiota of patients, such as gender, body mass index, TB severity, age, morbidities and so on [28]. Then using GLM to estimate the dynamic changes of microbiota composition with the control of selected confounders [29]. Differential abundance analysis of ASVs will be carried out using STAMP [30] and *p*-values will be adjusted for multiple testing (FDR-adjusted Wald Test). Correlations between clinical parameters and bacterial genera will be calculated using canonical correspondence analysis or redundancy analysis [31]. Random forests approach will be performed to find the most important species as marker taxa correlating with unfavorable treatment outcomes. The data will be analyzed using the QIIME2 pipeline and R [32]. A *p*-value or q-value ≤0.05 will be considered as statistically significant.

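### TB patients come from three regions and healthy controls from two, and the baseline comparison is not restricted to the shared regions or stratified by region, so regional differences can be mistaken for a TB effect

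*Protocol article*

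**What the plan says.** All references are to the protocol article.

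- **Patients.** Under Settings, "patient recruitment for this study will take place at three geographic locations, i.e. Sichuan province, Jiangsu province, and Shanghai". Under Sample size, "each site should enroll 50 eligible TB patients every year so that a patient cohort of 300 cases is expected within 2 years". That is about 100 patients per region.
- **Controls.** Under Sample size, "Healthy controls will be equally recruited from the population taking routine health check-up in Sichuan and Shanghai with a total amount of 60". That is 30 from each of two regions and none from Jiangsu.
- **The comparison.** Under Study design, "A comparison of gut microbiota will be performed between newly diagnosed TB patients and healthy controls to reflect the difference in baseline features". The second of the secondary objectives describes the same contrast. Neither place limits the patients by region.
- **Analysis.** The Microbiome analysis section names the Wilcoxon test for two-group comparisons and the Adonis test for beta diversity, and mentions no region term or stratum. The generalized linear model concerns factors affecting the microbiota of patients. Its example covariates, "such as gender, body mass index, TB severity, age, morbidities and so on", do not name site.
- **Why region matters.** The Background says of the gut microbiota that "its composition is also affected by many factors such as geography, diet, season, lifestyle, disease state", and in particular antibiotic use, influence it. Settings gives differences in diet, economy and TB epidemic as the reason for using three locations.

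**The concern.** The two groups differ by design in a factor that the protocol itself calls influential. One third of the expected patients come from a region with no controls, and the remaining regions carry different weights in the two groups. If all patients are compared with all controls, as the text reads, any regional difference in diversity or composition enters the TB-versus-control contrast. Recruiting more patients does not reduce this bias.

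What is at stake is the second secondary objective, and with it the role that the abstract gives the controls as the reference for the patients' microbiota. Adding a site covariate later cannot fully repair the design. Without Jiangsu controls, Jiangsu patients carry no within-region information on TB versus health, unless one assumes that the TB effect there equals the effect elsewhere.

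**Working it through.** **Inputs from the Sample size section.** Patients: 50 per site per year × 2 years = 100 per site, 300 in total. Controls: 60, split equally, so 30 in Sichuan and 30 in Shanghai. Assumed dysbiosis rates: 20% in patients and 5% in controls. Stated power: over 85% with 200 versus 60 at the 5% level (two-sided taken here, as the sidedness is not stated).

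**1. The plan's own power figure.** Use the normal approximation with pooled variance under the null.

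- Pooled rate = (200 × 0.20 + 60 × 0.05)/260 = 0.1654.
- SE under the null = √[0.1654 × 0.8346 × (1/200 + 1/60)] = 0.0547.
- SE under the alternative = √[0.20 × 0.80/200 + 0.05 × 0.95/60] = 0.0399.
- Power = Φ[(0.15 − 1.96 × 0.0547)/0.0399] = Φ(1.07) = 85.8%.

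The stated figure is reproduced. With all 300 patients against 60 controls, the same formula gives 89.0%.

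**2. Where the 200 could come from.** Two sites × 100 = 200. This matches the two regions that supply controls, but no sentence makes the link.

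**3. Expected region mix.**

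| | Sichuan | Jiangsu | Shanghai |
|---|---|---|---|
| All 300 patients | 1/3 | 1/3 | 1/3 |
| 60 controls | 1/2 | 0 | 1/2 |
| Sichuan and Shanghai patients only (200) | 1/2 | 0 | 1/2 |

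**4. Bias when TB has no effect.** Let d be a regional shift in a continuous diversity index, in units of the within-region SD. The document gives no value for d, so 0.3, 0.5 and 0.8 are assumptions.

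*Scenario A: Jiangsu differs from both other sites by d.*
- Bias = d × (1/3 − 0) = d/3.
- SE = √[(1 + 2d²/9)/300 + 1/60]. The term 2d²/9 is the between-region variance among patients, (1/3)(2/3)d².

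*Scenario B: Jiangsu resembles Shanghai, and Sichuan differs from both by d.*
- Absolute bias = d × (1/2 − 1/3) = d/6.
- SE = √[(1 + 2d²/9)/300 + (1 + d²/4)/60]. The term d²/4 is the between-region variance among controls, (1/2)(1/2)d².

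In both scenarios the false-positive rate is P(|Z + bias/SE| > 1.96).

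| d (SD) | A: bias | A: SE | A: false-positive rate | B: bias | B: SE | B: false-positive rate |
|---|---|---|---|---|---|---|
| 0.3 | 0.10 | 0.142 | 10.9% | 0.05 | 0.143 | 6.4% |
| 0.5 | 0.17 | 0.142 | 21.7% | 0.08 | 0.146 | 8.8% |
| 0.8 | 0.27 | 0.143 | 46.2% | 0.13 | 0.152 | 14.2% |

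**5. Cost of restriction.** SE with 200 versus 60 = √(1/200 + 1/60) = 0.1472 SD. With 300 versus 60 it is √(1/300 + 1/60) = 0.1414 SD. The ratio is 1.04, so about 4% wider. With both groups split 50:50 by region, the regional bias is zero in expectation.

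**The case against.** The strongest reply is that the remedy may already be intended. The Sample size section names Sichuan and Shanghai as the sources of controls and in the next sentence powers the comparison on 200 patients, exactly two sites' worth. On that reading the region mix is balanced and the bias disappears. This is plausible, but the reader has to infer it. The objectives and the Study design section speak of TB patients without limit, so the restriction still needs to be stated.

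Second, Settings describes Jiangsu as a neighbour of Shanghai with similar taste in food, and Sichuan as the contrasting site. That fits scenario B, with half the bias. TB notification does differ between Jiangsu and Shanghai (33.52 versus 14.75 per 100,000), so scenario A is not excluded. Both belong in the range.

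Third, the article is condensed. The covariate list is open-ended, Adonis is not said to be unadjusted, and the first secondary objective treats region as a descriptive factor among patients. A fuller plan may include site. This weakens any claim that site is deliberately left out. It does not change where the controls are recruited, which this document fixes.

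A reader might infer that any TB-versus-control difference will be regional and cannot be attributed to TB. The documents do not support that: the bias is a third or a sixth of an unknown shift, and a difference much larger than that would survive it.

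A reader might also infer that the choice of controls at health check-ups is itself a defect needing close age-band matching, or that sampling season must enter every model. Controls come from the local population, with the same age limits and largely the same exclusions as patients. No age or sex imbalance can be quantified from the text, and season is separate from the regional mismatch.

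**Conclusion.** The point holds as a design and wording weakness in one secondary objective. Read as written, the comparison sets a 33/33/33% regional mix against 50/0/50%, so regional differences can be mistaken for a TB effect. Across the assumed shifts of 0.3 to 0.8 SD, the false-positive rate lies between about 6% and 46%, depending on the size of the shift and on which region differs. The figures rest on equal accrual per site, no true TB effect, and a normal approximation for a continuous index. If regional differences are small, so is the bias. The stated power is correct, and the primary within-patient longitudinal objective does not use the controls. The correction is worth making because it costs little and may only put into words what the authors meant.

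**What to change.** State in the objectives, Study design and Microbiome analysis sections that the baseline TB-versus-control comparison uses patients from Sichuan and Shanghai only, 200 versus 60 as the power sentence already assumes.

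Analyse it by site: include a site term in the regression and permute within site strata for Adonis. Add age and sex as covariates. Study procedures already provides for socio-demographic data on patients and controls, so no new data are needed. Site stratification remains useful after restriction, because actual accrual may not be equal across the two sites.

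Cost: Jiangsu patients leave this one comparison and stay in every other analysis. The standard error is about 4% wider, and power for 20% versus 5% is 85.8% instead of 89.0%, still in line with the stated figure. If a three-region comparison is wanted instead, controls must also be recruited in Jiangsu. Thirty more (300 versus 90) would give 97.3% power by the same formula, at the cost of that recruitment.

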**Methods:**

The study is a multicenter, observational prospective cohort study. Three study sites are purposively selected in the western (Sichuan Province) and eastern (Jiangsu Province and Shanghai) parts of China. Three-hundred patients with bacteriologically confirmed pulmonary TB are enrolled. All eligible patients should be investigated using structured questionnaires before treatment initiation; and be followed up during the treatment at Day-14, Month-2, Month-5, the end of treatment and the sixth month after ending therapy. Stool samples are to be collected at each visit, consisting of six stool samples from each patient. Additionally, 60 healthy volunteers from Sichuan province and Shanghai city will be recruited as healthy controls to form the baseline of patient gut microbiota in the Chinese population. The dynamic changes of gut microbiota in terms of alpha diversity, beta diversity, taxonomic composition are to be illustrated individually from the time at diagnosis until the sixth month after therapy is completed. Furthermore, the diversity and component of gut microbiota will be compared between the groups with and without unfavorable treatment outcome in terms of adverse effect and treatment failure.

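### Controls come from two of the three patient sites, and the article does not say which patients enter the patient-control comparison or that site is accounted for

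*Protocol article*

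**What the plan says.** On patients, the Settings section says that "patient recruitment for this study will take place at three geographic locations, i.e. Sichuan province, Jiangsu province, and Shanghai". The Sample size section sets equal accrual: "each site should enroll 50 eligible TB patients every year so that a patient cohort of 300 cases is expected within 2 years".

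On controls, the same section says "Healthy controls will be equally recruited from the population taking routine health check-up in Sichuan and Shanghai with a total amount of 60", and the Abstract agrees: "60 healthy volunteers from Sichuan province and Shanghai city will be recruited as healthy controls". No control comes from Jiangsu.

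On the comparison, the Study design section says "A comparison of gut microbiota will be performed between newly diagnosed TB patients and healthy controls to reflect the difference in baseline features". Secondary objective 2 likewise sets TB patients at baseline against healthy controls. Neither text limits the patients by site.

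On the analysis, the Microbiome analysis section names the Wilcoxon test for two-group comparisons and Adonis for beta diversity, with no site term or stratification. The covariates listed for the generalized linear model do not include site. That list is open-ended and concerns factors acting on patients.

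On size, the Sample size section says "By assuming the rates of intestinal flora dysbiosis are 20% in TB patients [11] and 5% [23] in healthy controls", and that "the sample size of 200 TB patients and 60 healthy controls has over 85% power". It does not explain why 200 patients are used when the cohort is 300.

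**The concern.** The Background says of the gut microbiota that "its composition is also affected by many factors such as geography, diet, season, lifestyle, disease state", and the Settings section gives differences between the regions in diet, economy and TB burden as the reason for choosing these sites. Site is therefore a likely confounder by the article's own account. A contrast of all patients with all controls would set a three-site group against a two-site group. About a third of the patients would have no control from their own region, and Sichuan would make up one third of patients but one half of controls. Read literally, the objective, the design text and the unadjusted tests lead to that contrast. A difference due to geography could then be reported as a difference due to TB.

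The 200 in the power sentence points the other way, towards a comparison limited to the sites that have controls. The text therefore supports two analysis sets for the same objective, and the choice between them should not be left until the data are seen.

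**Working it through.** **Inputs from the article.** 50 patients per site per year for 2 years; three patient sites; 60 controls split equally between Sichuan and Shanghai, so 30 each; dysbiosis rates of 20% and 5%; 5% significance level (two-sided assumed, since sidedness is not stated).

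**Assumptions, not from the article.** Accrual meets the target at every site; TB has no effect; the outcome is an alpha-diversity index with within-group SD 1; the extra spread that site differences add within a group is ignored. The Jiangsu shift, d, is Jiangsu minus the average of Sichuan and Shanghai, and is varied over 0.2 to 0.5 SD.

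1. **The stated power, 200 v 60.** Pooled rate = (200 × 0.20 + 60 × 0.05)/260 = 0.1654. Standard error under the null = √[0.1654 × 0.8346 × (1/200 + 1/60)] = 0.0547. Standard error under the alternative = √(0.16/200 + 0.0475/60) = 0.0399. Power = Φ[(0.15 − 1.96 × 0.0547)/0.0399] = Φ(1.07) = 85.8%. This reproduces the stated figure of over 85%. The same formula with 300 v 60 gives 89.0%.

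2. **Where 200 could come from.** Two sites × 50 × 2 years = 200; three sites × 50 × 2 years = 300. The 200 matches the expected number of patients at the two sites that supply controls. This is an inference, because the article does not explain the figure.

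3. **Bias if all patients are compared unadjusted.** Let S, H and J be the Sichuan, Shanghai and Jiangsu means. Patient mean = (S + H + J)/3 and control mean = (S + H)/2. The difference is J/3 − (S + H)/6 = (1/3)[J − (S + H)/2] = d/3.

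4. **False rejection in that case.** Standard error (300 v 60) = √(1/300 + 1/60) = 0.141 SD. Rejection = 1 − Φ(1.96 − bias/SE) + Φ(−1.96 − bias/SE).

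| Assumed d (SD) | Bias d/3 (SD) | Bias/SE | Rejection at nominal 5% |
|---|---|---|---|
| 0.2 | 0.07 | 0.47 | about 8% |
| 0.3 | 0.10 | 0.71 | about 11% |
| 0.5 | 0.17 | 1.18 | about 22% |

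5. **Shared sites only.** Patients are 100 + 100 and controls 30 + 30, so both groups are split 50:50 and the bias from Jiangsu is zero. Standard error (200 v 60) = √(1/200 + 1/60) = 0.147 SD. The ratio is 0.147/0.141 = 1.04.

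6. **All sites with an additive site term.** The Jiangsu indicator is estimated from Jiangsu patients alone, so the TB coefficient comes from Sichuan and Shanghai. In a linear model with no other covariates it equals the two-site, site-adjusted estimate, and the Jiangsu shift drops out.

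**The case against.** Four points can be made on the other side.

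- **The 200 may already mean the two shared sites.** A reader might infer that the comparison is definitely run on all patients and that a Jiangsu difference is counted as a TB effect. The documents do not support that: the only sizing of this comparison uses a number that fits a two-site analysis. What stands is that the article never says so, while the objective and the design text read as all patients.

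- **Ordinary adjustment solves it.** A reader might infer that the missing Jiangsu controls put the problem beyond any adjustment. That is wrong, as step 6 shows. What remains is that no site term is named for this comparison. The covariates and analysis set of a secondary comparison are often left to an analysis plan, and this article is condensed. But it does fix the patient sites, the control sites, the comparison and the tests, and these do not fit together without a further sentence.

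- **The shift may be small.** The Settings section describes Jiangsu as adjacent to Shanghai and similar to it in taste, and Table 1 places Jiangsu between the two control sites on all four indicators. If Jiangsu equalled Shanghai, d would be half the Sichuan–Shanghai gap, so a 0.5 SD shift would need a 1.0 SD gap. If Jiangsu lay exactly midway, the bias would be zero. This stands, and the table above is a range of assumptions, not an estimate. Nor do the documents support a claim that Adonis would declare a TB effect on a slight regional shift. Such rejection rates depend heavily on how variance is assumed to spread across the taxa, which the article does not give.

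- **The reach is limited.** Only one secondary baseline comparison is affected. The primary longitudinal objective and the outcome analyses do not use controls. This stands too.

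**Conclusion.** The site mismatch is on the page, and the article states neither which patients the controls are compared with nor that site is accounted for. If all patients were compared unadjusted, one third of the difference between Jiangsu and the average of the two control sites would enter the TB contrast: 0.07 to 0.17 SD for assumed shifts of 0.2 to 0.5 SD, with rejection of about 8% to 22% at a nominal 5%. This rests on equal accrual at the three sites and on shift sizes that the documents do not supply. It shows what an unadjusted all-site analysis could do, and does not show that the study will be biased. The point deserves correcting because geography is a determinant by the article's own account and the remedy costs almost nothing.

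**What to change.** Add one statement to secondary objective 2 or to the Microbiome analysis section: the patient-control comparison uses Sichuan and Shanghai patients, compared within site. In practice this means site as a covariate in models, a site-stratified version of the Wilcoxon test, and Adonis permutations restricted to within site. In the Sample size section, say that the 200 patients are those expected from these two sites.

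Show the all-site contrast only as a site-adjusted sensitivity analysis. In a plain linear model it returns the same TB estimate, so it adds little beyond a check once other covariates are included. Describe Jiangsu patients' baseline microbiota separately, and keep them in all longitudinal and outcome analyses.

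The cost is a standard error about 4% larger for this one comparison (0.141 to 0.147 SD) than with all 300 patients. Against the article's own calculation there is no loss, since 200 v 60 is already the powered size (85.8%). No further patients, controls or samples are needed.
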